#### **G. Statistical Analysis**

Continuous variables were presented as mean (SD) or median (interquartile range, [IQR]), depending on whether the data was distributed normally or not. Categorical variables were presented as a number (percentage). The normal distribution of data was evaluated using the Shapiro–Wilk test, and the Levene method was used to test the homogeneity of variance. Differences in repeated measures variables were analysed by repeated-measures analysis of variance. Continuous outcomes were

analysed with one-way analysis of variance (ANOVA) or Kruskal-Wallis test. Categorical variables were tested using  $\chi^2$  test or Fisher's exact test. The primary analyses were performed according to the intention-to-treat (ITT) principle. Modified ITT (mITT) and per-protocol (PP) analyses were also performed as sensitivity analyses for the primary outcome. Results of primary and secondary outcomes were reported as relative risk (RR) or between-group difference with 95 % CI, the absolute risk reduction (ARR) and Number needed to Treat (NNT) were also calculated, with 95% CI. Kaplan-Meier curves were used for the time to first experience hypoxaemia. When an overall intervention effect was detected ( $P < 0.05$ ), the Bonferroni correction for multiple pairwise comparisons would be performed. To handle missing data, multiple imputations by chained equations was used, assuming missing data are missing at random. Imputation for continuous data was performed by predictive mean matching, logistic regression for binary variables. The number of imputations was 5. Convergence of the multiple imputation algorithm and the results of the imputation were checked. Imputations were performed with the R MICE package (J Stat Software. 2011;45(3):1–67.). Analyses were then performed on each of the imputed data sets and pooled according to Rubin's rules. As a post hoc sensitivity analysis, we used a logistic regression model simultaneously entering: age, BMI, current smoking status, chronic pain needing opioids, ARISCAT score (Assess Respiratory Risk in Surgical Patients in Catalonia), CCI (Charlson Comorbidity Index), surgery time, intraoperative opioid consumption, and the use of a nasogastric tube. R version 4.1.1 was used for statistical analysis, and analysis items with 2-sided  $P < 0.05$  were considered statistically significant.

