## H. Intervention

At the end of operation, patients were transferred from operating table to transfer bed, and their positions were adjusted according to the groups.

supine position group (group S): Patients were placed in supine position from the end of surgery to leaving PACU.

15-degree semi-recumbent position group (group F): Patients were placed in 15-

---

degree semi-recumbent position from the end of surgery to leaving PACU.

30-degree semi-recumbent position group (group T): Patients were placed in 30-degree semi-recumbent position from the end of surgery to leaving PACU.

The inclination angle was set precisely by an inclinometer (GeeLii 55157, Shanghai GeeLii International Trade Co., China)

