## **J. Measurements and Endpoints**

The primary outcome was the incidence of postoperative hypoxaemia in the PACU (defined as  $\text{SpO}_2 < 90\%$  for more than 10 seconds or  $\text{PaO}_2:\text{FiO}_2$  ratio below 300 mmHg). We also recorded the incidence of severe hypoxaemia ( $\text{SpO}_2 < 85\%$  for more than 10 seconds) and the time to first episode of hypoxaemia. Patients were continuously monitored real-time vital signs in the PACU using a Mindray BeneVision N15 monitor (Shenzhen Mindray Bio-Medical Electronics Co., Ltd.). In this study, data collection was performed by one-on-one researchers in the PACU, review of the monitor's database by the data collector when the patient leaving the PACU. To avoid pulse oximeter probe dislodging the finger or having it only partially on the finger, we used disposable finger probes that stick to the finger like a Band-Aid for continuous monitoring (Disposable  $\text{SpO}_2$  Sensor, Shenzhen Mindray Bio-Medical Electronics Co., Ltd.).

The secondary outcomes included:

airway rescue (defined as the need for mask noninvasive positive pressure ventilation, or re-intubation);

respiratory symptoms (coughing);

extubation time (defined as the time from end of surgery to extubation);

respiratory comfort (before leaving PACU, graded using a numerical rating scale, ranging from 0 to 10, higher score means more comfort);

duration of stay in the PACU;

wound pain (VAS score measured at rest, while coughing at 5 and 30 minutes after extubation, before leaving PACU, and 24 hours post operation);

and position-related adverse events (hypotension, arrhythmia, and some other adverse events).

The patient's vital signs (heart rate and mean arterial pressure) were recorded at six time points: (1) the beginning of surgery (T0); (2) the end of surgery (T1); (3) immediately after adjusting position (T2); (4) immediately prior to extubation (T3); (5) 1 min after extubation (T4); (6) when leaving the PACU (T5).

Dynamic lung compliance ( $\text{C}_{\text{dyn}}$ ) and driving pressure ( $\Delta P$ ) were also recorded at

---

320 three time points: (1) when stitching; (2) 5 minutes after adjusting position; and (3)  
321 before extubation.

322 Arterial blood gas analysis was performed at three time points: (1) when stitching; (2)  
323 5 minutes after adjusting position; (3) 5 minutes post-extubation.

324

---

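### Repeated-measures ANOVA without baseline adjustment makes poor use of the pre-position readings: it dilutes a position effect if the group main effect is tested and loses efficiency if group-by-time is tested

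*Protocol*

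**What the plan says.** Protocol section III.G gives one rule for all repeated variables: "Differences in repeated measures variables were analysed by repeated-measures analysis of variance". It names no baseline covariate, does not say which time points enter as responses, and does not say whether the group or the group-by-time term is tested. Its only decision rule, written for outcomes in general, makes Bonferroni-corrected pairwise tests conditional on an overall effect of the intervention at P < 0.05.

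Section III.H starts the intervention after the operation, on the transfer bed, where "their positions were adjusted according to the groups".

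Section III.J lists the readings:
- **Heart rate and mean arterial pressure (MAP):** six points, starting with "1) the beginning of surgery (T0); (2) the end of surgery (T1); (3) immediately after adjusting position (T2"). T0 and T1 precede positioning; T2 to T5 follow it.
- **Dynamic compliance and driving pressure:** three points, "1) when stitching; (2) 5 minutes after adjusting position; and (3") before extubation. The first precedes positioning.
- **Blood gases:** "Arterial blood gas analysis was performed at three time points: (1) when stitching; (2") 5 minutes after positioning and (3) 5 minutes after extubation. Again the first precedes positioning.
- **Wound pain:** repeated, but only after positioning, for example "while coughing at 5 and 30 minutes after extubation".

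**The concern.** A reading taken before the patient is tilted cannot show an effect of tilting. Its proper use is as a baseline that explains between-patient variation. Repeated-measures ANOVA in its plain form has no such role for it and treats every listed reading as a response. The group main effect then averages over times at which the true difference is zero. The group-by-time term avoids that averaging, but it spreads the comparison over all time differences, including the change from T0 to T1, which position cannot influence.

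The stated objective covers efficacy and safety. MAP after tilting is supporting evidence on safety; compliance, driving pressure and blood gases are supporting evidence on how tilting might act on the lungs. A needlessly weak test of these measures could return no difference and be read as reassurance or as evidence against a lung effect. If the overall test also gates the pairwise comparisons for these variables, a missed overall effect means that no pairwise comparison follows.

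**Working it through.** **Plan's own figure.** The protocol gives no figure for the repeated-measures analyses. Its sample size reproduces: 46% against 34%, 2:1, two-sided 5%, 80% power, continuity-corrected, gives 207 + 414 = 621 against the stated 620. This does not bear on the point, except that 620/3 gives about 206 per group for the power figures below.

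**Inputs from section III.J.** Vital signs: a = 2 readings before and b = 4 after positioning, k = 6. Compliance, driving pressure, blood gases: a = 1, b = 2, k = 3.

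**Assumptions (not in the protocol).** Unit variance, compound symmetry with correlation ρ, and an effect that is constant across the post-position points.

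**Step 1: dilution in the group main effect.** The effect is multiplied by b/k: 4/6 = 0.667 and 2/3 = 0.667.

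**Step 2: degrees of freedom of group-by-time.** (3−1)(6−1) = 10 for vital signs; (3−1)(3−1) = 4 for the three-point variables.

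**Step 3: efficiency of baseline adjustment against the main-effect test.**
- V_main = (1 + (k−1)ρ)/k
- V_adj = (1 + (b−1)ρ)/b − ρ²/V_pre, with V_pre = 1 for a single covariate reading and (1+ρ)/2 for the mean of T0 and T1
- Ratio = V_main / [(b/k)² × V_adj], with (b/k)² = 0.4444

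| Variables, covariate | ρ | V_main | V_adj | Ratio |
|---|---|---|---|---|
| Vital signs, T1 alone | 0.4 | 0.50 | 0.55 − 0.16 = 0.39 | 2.9 |
| Vital signs, T1 alone | 0.7 | 0.75 | 0.775 − 0.49 = 0.285 | 5.9 |
| Vital signs, mean of T0 and T1 | 0.4 | 0.50 | 0.55 − 0.16/0.70 = 0.321 | 3.5 |
| Vital signs, mean of T0 and T1 | 0.7 | 0.75 | 0.775 − 0.49/0.85 = 0.199 | 8.5 |
| Three-point, stitching value | 0.4 | 0.60 | 0.70 − 0.16 = 0.54 | 2.5 |
| Three-point, stitching value | 0.7 | 0.80 | 0.85 − 0.49 = 0.36 | 5.0 |

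The ratios do not depend on the size of the effect, only on its being constant.

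**Step 4: power of all three approaches.** Simulation with 2,000 runs, three groups of 206, and an assumed shift of 0.25 SD in both tilted groups. The adjusted analysis of vital signs used the mean of T0 and T1.

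| Variables | ρ | Main effect | Group-by-time | Baseline-adjusted |
|---|---|---|---|---|
| Vital signs | 0.3 | 0.78 | 0.80 | 1.00 |
| Vital signs | 0.5 | 0.63 | 0.94 | 1.00 |
| Vital signs | 0.7 | 0.50 | 1.00 | 1.00 |
| Three-point | 0.3 | 0.67 | 0.61 | 0.95 |
| Three-point | 0.5 | 0.56 | 0.78 | 0.97 |
| Three-point | 0.7 | 0.50 | 0.96 | 0.99 |

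The group-by-time test was at or below the adjusted analysis in every scenario. The gap is large for the three-point variables at low ρ and negligible for vital signs at high ρ.

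**Step 5: a brief effect.** If the effect is present at T2 only, the main effect carries 1/6 of it and the post-position mean 1/4. An average is then the wrong summary under either analysis, which is why the fix asks for contrasts by time point.

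**The case against.** The strongest reply is that the protocol names no tested term and does not say that the early readings enter as responses. Those details are commonly left to an analysis plan, which is not shown here. In a design with readings before and after the intervention, group-by-time is the natural test, and it uses the early readings as a within-patient reference. This largely stands. A reader might infer that the plan certainly dilutes the position effect; the text does not support that. The general rule about an overall intervention effect is compatible with a main-effect test but does not name one.

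A reader might also infer that the safety conclusion rests on this analysis. It does not. Hypotension and arrhythmia are position-related adverse events in the secondary-outcome list, and section III.G compares categorical variables by χ² or Fisher's exact test. Heart rate, MAP, lung mechanics and blood gases are recorded measures outside that list. The primary outcome is a binary incidence, and every wound-pain reading follows positioning. Nor does including early readings in itself create false positives.

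Finally, the 3.5 to 8.5 range belongs only to adjustment for the mean of T0 and T1. For T1 alone the range is 2.9 to 5.9.

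What the reply does not remove is that the protocol does state a method, and that this method has no baseline adjustment although a pre-position reading exists for each of these variables. Under either candidate term, the adjusted analysis was at least as powerful in every scenario examined.

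**Conclusion.** The point holds as a worthwhile improvement to the analysis of supporting physiological measures. One third of the readings precede positioning. The cost depends on a term that the protocol does not name:
- **Group main effect, all readings as responses:** a constant effect shrinks to two thirds. Baseline adjustment is 2.9 to 5.9 times as efficient for vital signs with T1 as covariate (3.5 to 8.5 with the mean of T0 and T1), and 2.5 to 5 times for the three-point variables.
- **Group-by-time:** no dilution, but some loss of efficiency. Power was 0.61 to 1.00 against 0.95 to 1.00 with adjustment, at an assumed 0.25 SD.

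The efficiency ratios assume compound symmetry, ρ of 0.4 to 0.7 and a constant post-position effect. The power figures use ρ of 0.3 to 0.7 and 206 per group. The protocol supplies neither a correlation nor an effect size for these variables.

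**What to change.** Replace the repeated-measures ANOVA sentence for these variables with a mixed model for repeated measures:
- **Responses:** post-position readings only, T2 to T5 for heart rate and MAP, and points 2 and 3 for compliance, driving pressure and blood gases.
- **Terms:** group, time and group-by-time.
- **Covariates:** the pre-position value (T1, or the mean of T0 and T1, chosen in advance; the stitching value for the three-point variables) and the stratification factors, type of surgery and age.
- **Reporting:** group contrasts with 95% CI at each time point, with the term that serves as the overall test named.

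Wound pain has no pre-position reading and needs no such covariate. The cost is a change of analysis wording; all values are already in the collection schedule.

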### *ii. Perioperative management*

Continuous monitoring was conducted for all patients through the use of electrocardiograms, noninvasive blood pressure measurements, bispectral index (BIS) electrodes (monitoring depth of anaesthesia), pulse oxygen saturation (SpO2) measurements, and end-tidal CO2 (ETCO2) measurements. Sufentanil 0.5 µg/kg, propofol 1.5 to 2.0 mg/kg, and rocuronium 0.8 mg/kg were used for anaesthesia induction. Anaesthesia was maintained with remifentanyl 0.1 to 0.3 µg/kg/min and propofol 4 to 12 mg/kg/h. After intubation, an arterial catheter was placed in the radial artery for blood gas sampling and invasive blood pressure monitoring. BIS value between 40 and 60 were maintained by adjusting the dose of propofol. The respiratory rate was initially set at 12 breaths/min and further adjusted to maintain end-tidal carbon dioxide pressure between 35 and 45 mmHg. Mechanical ventilation was maintained in a volume-controlled mode. Lung protective ventilation was used during surgery (the combination of tidal volume 8 ml/kg predicted body weight or lower and PEEP 5 cm H2O or higher, with a recruitment manoeuvre, fraction of inspired oxygen 60%) in all patients. Mean arterial pressure was maintained within ±20% of the baseline. Hypotension was treated with phenylephrine 40 µg, ephedrine 5 mg, or a fluid bolus; episodes of hypertension were managed by increasing the propofol or remifentanyl infusion rate. If the heart rate was less than 40/min, atropine 0.5 mg (i.v.)

was administered. The type and volume of fluid infusion were determined by the anesthesiologist. Rocuronium was continuously infused at a rate of 0.3 to 0.8 mg/kg/h and stopped approximately 40 minutes before the end of surgery. Postoperative patient-controlled intravenous analgesia (PCIA) was administered (sufentanil 2 µg/kg, tropisetron 10 mg, 0.9% saline diluted, the total volume of the solution is 100 ml.) and was set at 0.5 ml/press with a 15 minutes locking time. Pain scores (Visual Analogue Scale, VAS score) were assessed by nurses in the PACU. Moderate pain (VAS score 4-6) was treated with hydromorphone 0.25 mg, and severe pain (VAS score 7-10) with hydromorphone 0.5 mg, with an aim to reduce pain scores to less than 4. Once the Aldrete score was greater than or equal to 9 out of 10, the patient was discharged back to the ward.

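### Kaplan-Meier is the wrong curve for an outcome observed only until a recovery-dependent PACU discharge; cumulative incidence with discharge as a competing event would match the endpoint

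*Protocol*

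**What the plan says.** All references are to the protocol, part III.

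- **Statistical Analysis (G):** "Kaplan-Meier curves were used for the time to first experience hypoxaemia". No time origin, censoring rule, horizon or test is attached to the curves. Categorical variables get a chi-square or Fisher's exact test, and outcomes are reported as relative risk or difference, with ARR and NNT.
- **Measurements and Endpoints (J):** "The primary outcome was the incidence of postoperative hypoxaemia in the PACU". An event is SpO2 below 90% for more than 10 seconds, or a PaO2:FiO2 "ratio below 300 mmHg". The section also records "the time to first episode of hypoxaemia".
- **How each component is seen (J):** for SpO2, "Patients were continuously monitored real-time vital signs in the PACU", and the monitor's database is reviewed as the patient leaves. Blood gases are taken at three set times: at stitching, then "5 minutes after adjusting position; (3) 5 minutes post-extubation".
- **Perioperative management (I.ii):** "Once the Aldrete score was greater than or equal to 9 out of 10, the patient was discharged back to the ward".
- **Secondary outcomes (J):** these include "duration of stay in the PACU".

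**The concern.** Kaplan-Meier treats a censored patient as someone who stays at the same risk as those still under observation. An event-free patient who leaves the PACU does not fit that in two ways.

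1. For an outcome defined by the PACU stay, discharge without hypoxaemia ends the possibility of the event. It is a competing event. The Kaplan-Meier curve answers what would happen if nobody were discharged, whereas the endpoint asks what happens during the stay that patients actually had.
2. Discharge follows recovery, so those who leave early are plausibly at lower risk than those who remain. Independence of censoring and prognosis is then doubtful as well.

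Position may affect stay, since the protocol measures it as an outcome, so arms can be followed over different windows.

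The event times are also mixed. An SpO2 event is timed at onset. An event seen only in the blood gas is timed at the sample, and the only scheduled sample after extubation is at 5 minutes. Such patients produce a step in the curve that reflects the sampling plan.

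At stake is how the time-to-event figure is read: as higher than the reported incidence, or as showing a timing difference that comes from discharge or sampling.

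**Working it through.** **The plan's own figure.** The protocol gives no number for the Kaplan-Meier analysis. The related figure is the sample size: 46% versus 34%, 2:1 allocation, two-sided 5%, 80% power, continuity correction. It reproduces: 207 supine × 3 = 621, or 413 exposed × 1.5 = 619.5, against the stated 620. Nothing below changes it.

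**Direction.** Let Y be the number at risk and dN the number of first events at time t. Then:

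- 1 − KM(t) = Σ KM(s−) · dN(s)/Y(s)
- cumulative incidence(t) = Σ S(s−) · dN(s)/Y(s)

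Here S is the proportion free of both hypoxaemia and discharge. Because S ≤ KM, the cumulative incidence never exceeds 1 − KM at the same time. They are equal only if no event follows the first discharge. Carried to the end of the stay, the cumulative incidence is the crude PACU proportion.

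**Size, one worked case.** Assumptions that are not in the protocol: stay T follows a Gamma distribution with mean 45 and SD 15 minutes (shape 9, scale 5), the hazard h is constant, and events are independent of stay. Full-stay incidence p satisfies p = 1 − E[exp(−hT)] = 1 − (1 + 5h)^−9.

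- p = 0.46: h = (0.54^(−1/9) − 1)/5 = 0.01417 per minute
- p = 0.34: h = (0.66^(−1/9) − 1)/5 = 0.00945 per minute

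1 − KM(t) = 1 − exp(−ht). Cumulative incidence(t) = ∫₀ᵗ h·exp(−hs)·P(T > s) ds. Number at risk per arm = (700/3) · P(T > t) · exp(−ht).

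| Full-stay incidence | Time (min) | 1 − KM | Cumulative incidence | At risk per arm |
|---|---|---|---|---|
| 46% | 30 | 34.6% | 33.8% | 129 |
| 46% | 60 | 57.3% | 45.1% | 15 |
| 46% | 90 | 72.1% | 46.0% | 0.5 |
| 34% | 30 | 24.7% | 24.1% | 149 |
| 34% | 60 | 43.3% | 33.2% | 21 |
| 34% | 90 | 57.3% | 34.0% | 0.7 |

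The gap is under one point at 30 minutes and 10 to 12 points at 60. The 90-minute row should not be used: only 0.7% of stays last that long under this model.

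**Size, range over assumptions.** A simulation assumed a median stay of 40 minutes (log-SD 0.3, minimum 10), 0 to 80% of events caught at the 5-minute gas, and event and stay either independent or linked by a shared frailty. At 60 minutes, 1 − KM was 0.50 to 0.63 for a full-stay incidence of 46%, and 0.37 to 0.48 for 34%. When all events came before the first discharge, there was no gap (0.461 against 0.461).

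**Sampling step.** With 50 to 80% of events found at the gas, the curve jumped at 5 minutes by about 0.17 to 0.27 (34% incidence) or 0.22 to 0.36 (46% incidence).

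**Differing stays.** With one constant hazard (0.0145 per minute), stay independent of risk, and median stays of 30, 40 and 50 minutes, crude PACU incidence was 36%, 45% and 52%, while 1 − KM at 30 minutes was 0.35 in all three. So when stay is unrelated to risk, a difference in stay moves the crude proportion but not the Kaplan-Meier curve at a fixed time. When low-risk patients leave first, the risk set becomes enriched with high-risk patients, more so in an arm that discharges sooner, and the Kaplan-Meier curves can separate too. That separation between arms was not quantified.

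**The case against.** The strongest reply is that the central fact is inferred. The protocol does not say that patients are censored at discharge, and censoring rules and time origins commonly belong in an analysis plan, which is not shown here. That stands: their absence is not a fault, and the point is conditional on the usual Kaplan-Meier convention. What the protocol does fix is the method, and for an outcome confined to the PACU the named method does not suit the way observation ends.

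Second, the curves are never used to estimate incidence. The primary outcome is a proportion with its own test and effect measures, and no log-rank test or hazard ratio is named. This also stands. A reader might infer that the curves invalidate the reported incidence or the primary result; the documents do not support that.

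Third, a reader might infer that the curve must overstate incidence by a large amount, such as 72% against 46%. The documents do not support that either. The stay distribution is assumed, almost nobody remains at 90 minutes, and the gap vanishes if events come early. The worked case also has event and discharge independent, so it shows a difference of estimand, not bias from informative censoring.

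Fourth, the assigned position lasts until the patient leaves the PACU, so incidence over the actual stay is a coherent primary estimand, and nothing in the protocol shows that stay differs by arm. Agreed. A fixed window is therefore offered only as a sensitivity analysis.

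Fifth, an SpO2-only curve describes one component of the composite. True, so it should be labelled as such and shown in addition.

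**Conclusion.** The point holds as an inexpensive improvement to a supporting analysis. If event-free patients are censored at discharge, the Kaplan-Meier complement is at or above the crude PACU incidence by the same time, and gas-only events carry a time set by the sampling schedule. In the worked case the excess is negligible at 30 minutes and 10 to 12 points at 60, when about 15 to 21 patients per arm are still at risk. These figures rest on an assumed stay distribution and hazard; the true gap could be nil. Whether differing stays would separate the arms depends on whether stay differs by position and is linked to risk, and the protocol gives no data on either. The primary test, RR, ARR, NNT and the sample size of 620 are not affected by the choice of Kaplan-Meier.

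**What to change.** In Statistical Analysis:

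1. Replace the Kaplan-Meier curve with a cumulative incidence curve for first hypoxaemia, timed from extubation, with event-free PACU discharge as a competing event. Carried to the end of the stay, it agrees with the crude proportion of events counted from extubation.
2. Show the continuously monitored component (SpO2 below 90% for more than 10 seconds) as its own curve, labelled as a component. Keep the composite as the primary endpoint, and note on its curve that gas-defined events are timed at the sample.
3. Add, as a sensitivity analysis only, incidence over a fixed window from extubation, for example 30 minutes, a time already used for pain scores. State how patients discharged before the window ends are counted.

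The cost is a little extra analysis and wording. Monitor records and PACU stay are already collected, so no new data, procedures or patients are needed. The downsides are small: the SpO2 curve does not describe the composite, the fixed window leaves out later events, and early discharges need the stated convention.

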#### **F. Sample Size Calculation**

The sample size for the primary outcome of this study was calculated with continuity correction, and was based on a ratio of exposed (combined 15-degree and 30-degree SRP) to unexposed (supine positioning) groups of 2:1. According to our pilot study, the frequency of hypoxaemia was 46% in the unexposed group, with a 26% relative (12% absolute) reduction in the exposed group. Assuming a two-tailed type I error rate of 5%, a sample size of 620 was needed to give greater than 80% power to detect a decrease in the incidence of hypoxaemia from 46% in the supine positioning group to 34% in the combined 15-degree and 30-degree SRP groups. Finally, we planned to recruit 700 patients to compensate for dropouts. The sample size calculation was conducted using the PASS 11.0 software (NCSS LLC).

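### For outcomes with exactly three pairwise comparisons, Bonferroni after a significant overall test is valid but unnecessary, and it costs power on the angle comparisons

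*Protocol*

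**What the plan says.** Section E of the protocol randomises 1:1:1 to supine, 15 degrees and 30 degrees. Section G analyses categorical outcomes, including the primary outcome, with a chi-square or Fisher's exact test. If the overall effect has P < 0.05, "the Bonferroni correction for multiple pairwise comparisons would be performed". The same section says that primary and secondary results "were reported as relative risk (RR) or between-group difference with 95 % CI", and it closes with a general two-sided 5% significance level. It does not state the number of pairs; three arms give three. It gives no reason for using both the gate and the correction.

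Section F sizes the trial for a different contrast. The calculation "was based on a ratio of exposed (combined 15-degree and 30-degree SRP) to unexposed (supine positioning) groups of 2:1", "was calculated with continuity correction", and concludes that "a sample size of 620 was needed to give greater than 80% power" for a fall from 46% "to 34% in the combined 15-degree and 30-degree SRP groups". Recruitment is raised to 700 for dropouts.

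**The concern.** The gate and the correction protect against the same multiplicity. With three groups, if any two of the pairwise null hypotheses are true, all three groups are equal, and the overall test already limits that case to 5%. If only one pair is truly equal, one true null hypothesis is left, and testing it at 5% needs no further division. Cutting each pairwise level to 0.05/3 = 0.0167 behind the gate pays for protection that is already there.

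The price falls on the comparisons that address the trial's question about angle. Section II.C says that evidence on a suitable tilt angle is lacking, and only the pairwise comparisons can supply it. Section F powers the pooled contrast alone, so these comparisons start with less power.

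Reporting is also affected. If the 95% confidence intervals are left unadjusted, a pair with P between 0.0167 and 0.05 will generally have an interval that excludes no effect while its test is called non-significant.

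**Working it through.** **Inputs.** From Section F: two-sided 5%; 46% supine; 34% combined semi-recumbent; 2:1 ratio; continuity correction; N = 620 (about 207 per arm); recruitment 700 (about 233 per arm). From Section G: overall gate at P < 0.05, then Bonferroni. Assumptions: 34% in each angle arm, because the protocol gives no per-angle rates; a 3×2 chi-square gate with 2 degrees of freedom; three pairs.

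**1. Reproduce the sample size.** With k = 2 and d = 0.12, the pooled rate is (0.46 + 2 × 0.34)/3 = 0.38.

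- Uncorrected supine n = [1.960·√(1.5 × 0.38 × 0.62) + 0.842·√(0.46 × 0.54 + 0.34 × 0.66/2)]² / 0.12² = (1.165 + 0.505)²/0.0144 ≈ 193.8. This rounds to 194, or 582 in total.
- Continuity correction: n′ = (n/4)·[1 + √(1 + 2(k+1)/(n·k·d))]² = (193.8/4)·[1 + √(1 + 6/46.5)]² ≈ 206.1. This rounds to 207, or 621 in total.

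The stated 620 is reproduced; continuity-corrected power at 620 is 80.1%.

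**2. One pair without the gate** (46% vs 34%, 620/3 per arm, mean rate 0.40). Power = Φ[(0.12 − z·√(0.48/206.7)) / √(0.4728/206.7)] = Φ[(0.12 − z × 0.0482)/0.0478].

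- At 5%, z = 1.960: Φ(0.534) = 70%.
- At 0.0167, z = 2.394: Φ(0.097) = 54%.

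**3. Gate followed by pairwise tests.** Simulation of 300,000 to 400,000 trials per scenario, chi-square tests without continuity correction, rates 46/34/34%:

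| Claim | 207/arm, pairs at 5% | 207/arm, Bonferroni | 233/arm, pairs at 5% | 233/arm, Bonferroni |
|---|---|---|---|---|
| One given angle vs supine | 65% | 54% | 71% | 60% |
| Both angles vs supine | 56% | 38% | 63% | 44% |
| At least one angle vs supine | 74% | 71% | 79% | 76% |

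The loss is about 11 points for one given angle and 18 to 19 for both. These are two different measures, not the ends of one range.

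**4. Unequal angle rates** (assumed: 46/37/31, 46/36/32, 46/38/30, 46/40/28). Over both sample sizes, the loss is 12 to 17 points for the weaker angle versus supine, 1 to 5 for the stronger angle, 7 to 16 for 15 versus 30 degrees, and 12 to 19 for both angles versus supine.

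**5. Family-wise error with the gate and 5% pairs.** It is 5.0–5.1% when all arms are equal. With two arms equal and the third different it is about 5%; the largest value over a grid of rates was 5.5%, which reflects the discreteness of the chi-square test. With gate plus Bonferroni it is about 4.2% when all arms are equal and 1.6–1.8% for the single true null pair at the design rates. Without any gate, 5% pairwise tests give about 12–13%, so the gate is essential.

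**6. Intervals and tests.** At 46/34/34%, the gate passes and at least one angle-versus-supine P value lies between 0.0167 and 0.05 in about 19–20% of trials. If pairs are tested at 5% behind the gate, this conflict largely goes. What remains is the case where the gate fails but some pair has P < 0.05: about 11% of trials at 207 per arm.

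**The case against.** The strongest reply is that nothing here is wrong. Gate plus Bonferroni controls the error rate. The hypothesis in Section II.C is semi-recumbent versus supine, the sample size rests on the pooled contrast, and neither is touched. Power to show at least one angle better than supine hardly moves. All of this stands: the point concerns efficiency, and a reader who inferred an invalid analysis or an undersized trial would go beyond the document.

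Three further limits also stand.

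- **Scope.** The Bonferroni sentence is not confined to the primary outcome. Section J records heart rate and mean arterial pressure at six time points, so three pairs at each would give 18 comparisons behind one gate. The three-group argument does not cover that, and one should not infer that the correction can be dropped everywhere.
- **Choice of gate.** The pooled contrast might seem a natural alternative gate. It controls error but can do harm: at 46/46/34% and 207 per arm, power for 30 degrees versus supine is 54% under the present rule, 64% with the overall gate and 5% pairs, and 30% with the pooled gate and 5% pairs.
- **Intervals.** The protocol does not say that pairwise intervals stay unadjusted, and an analysis plan may settle it. Nor would the change make intervals and tests agree always; they agree broadly, and only once the gate is passed.

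The size depends on the assumption of three pairs. If only the two angle-versus-supine pairs were corrected (0.025 each), the loss for one angle would be about 6–7 points.

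**Conclusion.** The point holds for the primary outcome and for any single-time-point outcome with exactly three pairwise group comparisons. There the Bonferroni step gives no protection that the stated 5% level requires. At 46/34/34% and 207 per arm it costs about 11 points of power for one given angle versus supine and 18 to 19 for showing both better than supine, but only about 3 for showing at least one. These figures assume equal rates in the two angle arms, a 2-df chi-square gate and three pairs. For 15 versus 30 degrees no single figure can be given: at equal rates there is no difference to detect, and otherwise the loss depends on rates the protocol does not state. The existing rule is conservative, not invalid, so this is a worthwhile improvement and not a correction of an error.

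**What to change.** Limit and replace the Bonferroni sentence in Section G, for example: *For the primary outcome and other outcomes assessed at a single time point, the three groups are first compared with an overall test at two-sided 5%. If it is significant, each of the three pairs is tested at two-sided 5%; if not, no pairwise claim is made. Where pairs are compared at several time points, a multiplicity correction is retained.*

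Name the three-group overall test as the only gate and do not offer the pooled contrast as an option. Add that if the gate fails, a 95% interval that excludes no effect supports no claim.

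The cost is a few lines of text, with no extra patients or data. The false-positive rate for a single true null pair rises from about 1.6–1.8% to about 5%, the level intended. Because the change relaxes a threshold, it must be fixed before outcomes are seen; after that, the Bonferroni rule should stand as the planned analysis.
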